### **8.2. Assessment phase definitions and special circumstances**

#### **8.2.1. Baseline**

Some patients in this study may have already commenced treatment with imatinib, while others will be treatment naive.

- Informed consent within 90 days
- Medical History, previous anti-cancer therapies and physical assessment
- ECG
- Blood collection for biochemistry including serum creatinine, urea, LFT, , calcium, magnesium, phosphate, TFT, full blood count including differential cell count and INR
- Note: If screening bloods are performed within 14 days of randomisation baseline bloods are not required.
- Urinalysis
- Pregnancy test
- ECG
- CT scan chest / abdominal / pelvis within 21 days of randomisation.
- Optional blood for research

#### **8.2.2. During treatment**

- Clinical assessment (including vital signs, blood pressure, physical examination, ECOG PS, adverse event monitoring), full blood count (including differential cell count), biochemistry (including serum creatinine, urea, LFT, calcium, magnesium, phosphate) to be performed for ARM A at the beginning of each cycle and at C1, C2 and C3 Wk 4 D1, for ARM B at the beginning of each cycle and at C1, C2 and C3 Wk 5 D1
- All participants who are on regorafenib should have their blood pressure monitored weekly from the commencement of regorafenib in cycle 1 until the end of cycle 2. During this time, participants must attend the clinic weekly for their blood pressure to be taken. Alternatively, the weekly blood pressure measurements can be done by GPs, or using home blood pressure monitors if available. Blood pressure readings collected by the patient at home or by their GP will need to be communicated to the study site for appropriate management. Recommendations for anti-hypertension management will be provided in the Study Manual.
- Liver function testing must also be performed weekly in the alternating treatment arm (Arm B) during regorafenib use for the first 2 cycles. INR should be checked at baseline and then as clinically indicated.
- Dipstick urinalysis using standard urine test strip is required on day 1 of each cycle. If abnormal, further investigations should be conducted as clinically appropriate.
- For patients on Arm A blood collection for drug (imatinib) level testing to be performed on cycle 1 week 4 and cycle 2 week 4. For patients on the alternating regimen (Arm B) blood collected for drug (imatinib) level testing to be performed on cycle 1, on last day of imatinib administration and cycle 2 on last day of imatinib administration. Blood collected for drug (regorafenib) level testing to be performed on cycle 1 week 7 (on last day of regorafenib) and cycle 2 week 7 (on last day of regorafenib).
- Blood for translational research will be collected at the following timepoints;
  - Baseline/screening
  - C1 Wk1 D1 (prior to the commencement of study treatment, Baseline)
  - For Arm A: C1 Wk4 and C2 Wk4.

# ALT GIST

- For Arm B: C1 on the last day of imatinib administration C1 Wk7 (on the last day of regorafenib administration)
- For Arm B: C2 on the last day of imatinib administration and C2 Wk7 (on the last day of regorafenib administration)
- C4, and 8 Wk1 D1
- Upon relapse
- For the first 12 months, CT scans are performed 8 weekly from randomisation after which CT scans are performed 12 weekly until progression.
- A select group of Arm B patients will be enrolled in the PET substudy – Arm B patients will be further randomised to have PET scans either during the imatinib washout period, or during the regorafenib washout period. PET will be carried out on 2 occasions in each group and will be performed in Cycle 2 at the earliest, or in a subsequent cycle (at the first opportunity after a complete cycle of treatment without dose modifications is given).

## ***8.2.3. End of treatment***

No additional investigations are required for this trial at the time of treatment cessation.

## ***8.2.4. 30 day safety assessment***

A safety assessment should be performed to include any adverse events occurring within 30 days (+/- 7 days) after the last dose of study treatment.

## ***8.2.5. Follow-up after treatment***

Subjects who stop study treatment prior to the time recommended in the protocol will continue follow-up visits.

If a patient wishes to stop the study visits, they will be requested to allow their ongoing health status to be periodically reviewed via continued study visits or phone contact or from their general practitioner, or medical records, state-based cancer registries and/or the national mortality registry.

## ***8.2.6. After study is closed***

The study will be closed after data required has been collected and analysed. Collection of long term outcomes, for example survival data, may continue after the main study is closed, using a simple follow-up CRF, monitoring of central registries, or contact with treating clinicians.

# **9. OUTCOMES, ENDPOINTS AND OTHER MEASURES**

## ***9.1. Objective tumour response (complete or partial response) at or before 9 months***

Tumour evaluation using the RECIST Version 1.1 guidelines will be used to determine response status (i.e. complete response, partial response, stable disease, and progressive disease) at each assessment time point. The OTRR will be calculated by summing the number of participants assessed as having a complete or partial response within the first 9 months from the time from either (i) randomization (if patients have not yet commenced treatment) or (ii) commencement of therapy (if patients are randomized during the first cycle of imatinib), and dividing this by the total number of participants evaluable for response. For patients who undergo surgery, the best response is determined in the time period that precedes the date of surgery

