## Assessments

- Clinic visits (including laboratory tests) will be required at baseline, prior to each cycle of treatment and at the end of study treatment visit. During Cycles 1, 2 and 3, clinic visits will occur prior to commencing each new agent (4 weekly) including blood tests for haematological, hepatic, thyroid and renal function.
- Additional liver function tests will be performed weekly during the first 2 cycles of regorafenib treatment for those patients in the alternating arm (Arm B) of the study.
- Imaging will be performed at baseline (within 21 days prior to randomisation) and every 8 weeks for the first year on trial, and then every 12 weeks until disease progression or death, timed from the randomisation date.
- Blood samples for biomarker studies will be collected at baseline. And in Arm B every 4 weeks for the first 2 cycles of treatment then at commencement of cycle 4, 8 and disease progression. And in Arm A in cycle 1,2, 4, 8 and disease progression.
- Blood for drug (imatinib) plasma level- will be collected in Arm A cycle 1 week 4 and cycle 2 week 4. For patients on the alternating regimen (Arm B) blood will be collected

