# Not suitable for surgery with curative intent

\* Patients who have already commenced imatinib may be randomized at any time in the first 25 days of treatment. For these patients, the number of days that imatinib has already been taken for will be **included** in the treatment period (ie this prior treatment will count towards the total days of imatinib in cycle 1).

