## ALT GIST

### 8. ASSESSMENT PLAN

#### 8.1. Schedule of assessments

Assessments must be completed within 3 days of the assessment due date (unless otherwise specified in the footnotes)

**ARM A IMATINIB ALONE** NB: 1 cycle in continuous treatment arm = 8 weeks of imatinib (56 days)

| Parameter                                        | Screening/
Baseline
(28 days prior to
randomisation) | Cycle 1        |         | Cycle 2 |         | Cycle 3 |         | Cycle 4 and ongoing
cycles         | 30 day
safety
assessment | Follow-up (12 weekly)                          |
|--------------------------------------------------|---------------------------------------------------------------|----------------|---------|---------|---------|---------|---------|---------------------------------------|--------------------------------|------------------------------------------------|
|                                                  |                                                               | Wk 1D1         | Wk 4 D1 | Wk 1D1  | Wk 4 D1 | Wk1 D1  | Wk 4 D1 | Wk1 D1                                |                                |                                                |
| Informed consent                                 | x a                                                |                |         |         |         |         |         |                                       |                                |                                                |
| Pregnancy test                                   | x                                                             | x d |         |         |         |         |         |                                       |                                |                                                |
| Clinical assessment b                 | x                                                             | x              | x       | x       | x       | x       | x       | x                                     |                                |                                                |
| Mutation status if not
previously determined  | x c                                                |                |         |         |         |         |         |                                       |                                |                                                |

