b: clinical assessment including vital signs, blood pressure, physical examination, ECOG PS,

c: analysis of tumour mutation status if not previously known does not need to be completed prior to randomisation

d: if screening bloods and urine tests are performed within 14 days prior to randomisation baseline bloods and urine are not required to be repeated

e: biochemistry including serum creatinine, urea, LFT, TFT, calcium, magnesium, phosphate. INR should be checked at baseline and then as clinically indicated

f: full blood count including differential cell count

g: dipstick urinalysis using standard urine test strip is required on D1 of each cycle. If abnormal, further investigations should be conducted as clinically appropriate

h: blood collected for drug (imatinib) level testing. Refer to Biological Sampling Handbook for details of collection and processing. Documentation of compliance with treatment during the preceding cycle should be documented in the eCRF

i: blood for **optional** translational research will be collected at these timepoints. Refer to Biological Sampling Handbook for details of collection and processing

j: for the first 12 months, CT scans are performed 8 weekly from randomisation after which CT scans are performed 12 weekly. Imaging of the brain should be undertaken if clinically indicated. CT scans should continue as per the protocol until PD

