### 3 Response Definitions

# ALT GIST

All participants will have their BEST RESPONSE from the start of study treatment until the end of treatment classified as outlined below:

**Complete Response (CR):** Disappearance of all *target* and *non-target* lesions and normalisation of any specified tumour markers. Pathological lymph nodes must have short axis measures < 10mm (**Note:** continue to record the measurement even if < 10mm and considered CR). Residual lesions (other than nodes < 10mm) thought to be non-malignant should be further investigated (by cytology or PET scans) before CR can be accepted. Confirmation of response is sometimes required in studies where objective tumour response is the primary endpoint, and the details of confirmation are then specified in the body of the protocol.

**Partial Response (PR):** At least a 30% decrease in the sum of measures for target lesions (longest diameter for tumour lesions and short axis measure for target lymph nodes), taking as reference the baseline sum of diameters. Non-target lesions must be non-PD. Confirmation of response is sometimes required in studies where objective tumour response is the primary endpoint, and the details of confirmation are then specified in the body of the protocol.

**Stable Disease (SD):** Neither sufficient shrinkage to qualify for PR nor sufficient increase to qualify for PD taking as reference the smallest sum of diameters on study.

**Progressive Disease (PD):** At least a 20% increase in the sum of diameters of measured lesions taking as references the smallest sum of diameters recorded on study (including baseline) AND an absolute increase of  $\geq 5$ mm. Appearance of new lesions will also constitute progressive disease (including lesions in previously unassessed areas). In exceptional circumstances, unequivocal progression of non-target disease may be accepted as evidence of disease progression, where the overall tumour burden has increased sufficiently to merit discontinuation of treatment or where the tumour burden appears to have increased by at least 73% in volume. Modest increases in the size of one or more non-target lesions are NOT considered unequivocal progression. If the evidence of PD is equivocal (target or non-target), treatment may continue until the next assessment, but if confirmed, the earlier date must be used.

**Table 1:** Integration of Target, Non-target and New lesions into response assessment

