| No Target                                                                                                                                                                                                                                                                                                                                                                                                                                                                                                                                                                                                                                                    | Any               | Yes | PD            |                                                                  |
| 
Note: Participants with a global deterioration of health status requiring discontinuation of treatment without objective evidence of disease progression at that time should be reported as “symptomatic deterioration”. This is a reason for stopping therapy, but is NOT objective PD. Every effort should be made to document the objective progression even after discontinuation of treatment.
 
*Confirmation of a complete or partial response will be undertaken based on the results of the next scan performed (i.e. no additional scans to those presented in the Schedule of Assessments in Section 6.1 are required).
 |                   |     |               |                                                                  |

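### The 9-month response cut-off falls days before the week-40 scan, so on schedule the primary endpoint measures response only to week 32

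*Protocol*

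**What the plan says.** Section 9.1 of the protocol builds the primary endpoint from "participants assessed as having a complete or partial response within the first 9 months". The clock starts at randomisation or, for patients already on treatment, at "commencement of therapy (if patients are randomized during the first cycle of imatinib"). The note to the Study Schema says that such patients "may be randomized at any time in the first 25 days of treatment".

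The scans run on a different clock. The synopsis, under Assessments, times imaging "every 8 weeks for the first year on trial, and then every 12 weeks until disease progression or death, timed from the randomisation date". The Arm A footnote in section 8.1 agrees: "for the first 12 months, CT scans are performed 8 weekly from randomisation after which CT scans are performed 12 weekly". The Arm B footnote and section 8.2.2 give the same interval. The general tolerance in section 8.1 is: "Assessments must be completed within 3 days of the assessment due date" unless a footnote says otherwise, and the CT footnotes give no other window.

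On confirmation, the footnote to Table 1 of Appendix 2 says: "Confirmation of a complete or partial response will be undertaken based on the results of the next scan performed", with no scans beyond the schedule. Section 3 of the same appendix notes that confirmation is sometimes required when response is the primary endpoint, and that "the details of confirmation are then specified in the body of the protocol". Section 9.1 does not mention confirmation.

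**The concern.** A cumulative response rate at a landmark can include only responses that a scan has shown by then. If the landmark falls shortly before a scheduled scan, the reported rate describes the previous scan, and the label overstates the follow-up. Here the cut-off and the scan schedule are both fixed in the protocol, and they miss each other by a few days.

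This has two consequences. First, a rate labelled 9 months would reflect response to about 7.4 months after randomisation, and a patient scanned a few days too early could be counted as a responder when an identical patient scanned on time could not. Second, a response first seen at the last usable scan is confirmed only after the cut-off, and section 9.1 does not say whether that is acceptable. Section 13.1 describes the measured activity as primarily descriptive, so the meaning of the reported rate is the main product of the trial.

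**Working it through.** **The plan's own figure.** The only calculated figure tied to this endpoint is the table in section 13.1: at least 7, 10, 13 and 17 responses of 38 for true rates of 30%, 40%, 50% and 60%. The smallest r with P(X ≤ r | n = 38, p) > 0.05 under the exact binomial is 7, 10, 14 and 18. That is within one response of the table, and nothing below depends on it.

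**Inputs.** Cut-off: 9 months (9.1). Scan interval: 8 weeks from randomisation in year 1 (synopsis, 8.1, 8.2.2). Window: 3 days either side (8.1). Lead of the clock over randomisation, L: 0 for untreated patients and up to 25 days for patients already on imatinib (Study Schema note, 9.1). Alternating arm: 38 patients (13.1).

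**Length of 9 months.** Counted from every start date over four years, nine calendar months spans 273 to 276 days, or 273.9 days (39.1 weeks) on average.

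**Scan days.** Scan k is due on day 56k + L of the endpoint clock, with a window of 3 days either side.

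| Scan | L = 0: due (window) | L = 25: due (window) | Inside 9 months? |
|---|---|---|---|
| Week 8 | 56 (53–59) | 81 (78–84) | yes |
| Week 16 | 112 (109–115) | 137 (134–140) | yes |
| Week 24 | 168 (165–171) | 193 (190–196) | yes |
| Week 32 | 224 (221–227) | 249 (246–252) | yes |
| Week 40 | 280 (277–283) | 305 (302–308) | no |

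This holds for every lead between 0 and 25 days. The earliest in-window week-40 scan is day 277 + L, which is at least 277 and so later than 276. The latest in-window week-32 scan is day 227 + L, which is at most 252 and so earlier than 273.

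**What the endpoint measures.** Week 32 is 224 / 30.44 = 7.4 months from randomisation. For a patient with 25 days of prior imatinib it is 249 / 30.44 = 8.2 months from the start of treatment. For an untreated patient the week-40 due date is 280 − 276 = 4 to 280 − 273 = 7 days too late, and at the earliest permitted date it is still 277 − 276 = 1 to 277 − 273 = 4 days too late.

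**Confirmation.** The next scan after week 24 (day 168 + L) is week 32 (day 224 + L), inside the window. The next scan after week 32 is week 40 (day 280 + L), outside it.

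**Size.** One patient of 38 is 1 / 38 = 2.6%. The documents do not say how many patients first respond at week 40. As assumptions only, shares of 2.6%, 5% and 10% of patients give 38 × 0.026 = 1.0, 38 × 0.05 = 1.9 and 38 × 0.10 = 3.8 responders not counted.

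**The case against.** The strongest reply is that an endpoint at or before 9 months needs no scan at 9 months. Any landmark falls on or between scans, four scheduled scans precede this one, and a response first seen on day 280 was not observed by 9 months, so excluding it merely applies the definition. That is correct: such patients are not responders wrongly left out under the present wording. But the label still does not describe what is measured, and a scheduled scan lies within a week of the cut-off and can be used at no extra imaging.

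A second reply is that responder status turns on early scanning only if scans deviate from the 3-day window, and nothing suggests that this will be common. That also stands. It limits how often the problem arises, but it leaves the primary endpoint open to a scheduling deviation.

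Third, the effect is modest against the precision. At 23 of 38 responders the exact 95% interval is about 43% to 76%, and the section 13.1 table gives counts consistent with various true rates, not decision limits. Scan timing is the same in both arms. So there is no ground for saying that a decision would change or that one arm is favoured.

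A reader might go further and infer that this is really a week-24 endpoint, because a week-32 response cannot be confirmed by 9 months. The protocol does not support that. It nowhere requires the confirming scan to fall within 9 months, and section 4 of Appendix 2 dates a response, for duration only, from when the criteria are first met. Nor is confirmation simply missing, because the Table 1 footnote gives a rule. What is missing is the statement in 9.1 of how that rule meets the cut-off. A reader might also worry about responders operated on before the confirming scan, since 9.1 counts only the period before surgery. That is an edge case of unknown frequency, arises only if confirmation is mandatory, and adds little here.

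**Conclusion.** The point holds as a mismatch between two items that the protocol itself fixes. On schedule, the week-40 scan can never count towards the 9-month response rate, and the last look is week 32, about 7.4 months from randomisation. This is calendar arithmetic and rests only on the 8-week interval, the 3-day window and calendar months. Only an out-of-window or unscheduled scan changes it.

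The confirmation part is narrower: a week-32 response is confirmed after the cut-off, and 9.1 should say that this is acceptable. A week-24 limit would follow only from an added condition that the protocol does not contain.

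The number of responders affected cannot be derived from the documents; the shares shown above are assumptions. The effect is on the level and meaning of the primary rate, not on the comparison of the arms. The change is worth making because it needs no additional scans.

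**What to change.** Define the primary endpoint by scheduled assessment: CR or PR first documented at or before the week-40 scan, due on day 280 and accepted to day 283 from randomisation under the existing 3-day window. Say openly that for patients already on imatinib this reaches up to day 283 + 25 = 308 from the start of imatinib, and bring the time origin in the synopsis and sections 3 and 9.1 into line.

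State in 9.1 that a response is dated at the first scan meeting the criteria, and that the confirming next scheduled scan may fall after the cut-off. For a week-40 response that scan is week 48 (day 336), still within the 8-weekly period. Report the strict 9-month calendar rate and the unconfirmed rate as sensitivity analyses.

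The cost is a protocol amendment to the endpoint wording, which under section 15.3 needs the International Steering Committee and ethics approval. Readout moves by about 1 week (283 − 276 = 7 to 283 − 273 = 10 days), plus up to about 8 weeks for confirmation of week-40 responses. No extra scans are needed.

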## 7.5. Subsequent treatment

Treatment after discontinuation of study treatment is at the discretion of the patient's clinician.

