## 13.2. Statistical Analysis

Analyses will include all patients who were randomised. Treatment activity will be assessed by the proportion, together with the 95% confidence interval, of patients having an objective response at or before 9 months. Similar proportions will be determined in the control group,

Time-to event endpoints of progression free and overall survival and time to treatment failure will be described using the method of Kaplan-Meier. Treatment failure is defined as the first event before 12 months of death, disease progression and unacceptable toxicity causing study treatment to cease or patient preference to cease therapy. For purposes of treatment failure, only events in the first 12 months will be considered. Patients not experiencing a treatment failure within 12 months will be censored at 12 months. While there will not be any formal comparisons between the two groups, exploratory comparative analyses may be performed. For time-to-event outcomes, these will include univariate logrank and multivariate proportional hazards comparisons. Other exploratory analyses will also be performed as appropriate.

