### 1 Evaluable for response

All participants who have received at least one cycle of therapy and have their disease re-evaluated will be considered evaluable for response (exceptions will be those who exhibit objective disease progression prior to the end of cycle 1 who will also be considered evaluable). Participants on therapy for at least this period and who meet the other listed criteria will have their response classified according to the definitions set out below.

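### Sections 9.1 and 13.2 give conflicting denominators for the primary response rate, and the evaluable-patient version is likely to overstate it

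*Protocol*

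**What the plan says.** Protocol section 9.1 defines the objective tumour response rate as the number of patients with a complete or partial response in the first 9 months, "and dividing this by the total number of participants evaluable for response". Section 9.3 builds the clinical benefit rate on the same kind of denominator. The synopsis and section 13.1 size the trial as 60 evaluable patients, 38 of them in the alternating arm (Arm B).

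Section 13.2 opens differently: "Analyses will include all patients who were randomised". It continues: "Treatment activity will be assessed by the proportion, together with the 95% confidence interval, of patients having an objective response", with no restriction to evaluable patients.

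Appendix 2, section 1 defines the evaluable set: "All participants who have received at least one cycle of therapy and have their disease re-evaluated will be considered evaluable for response". It adds that "exceptions will be those who exhibit objective disease progression prior to the end of cycle 1 who will also be considered evaluable". The note to Table 1 of that appendix says of symptomatic deterioration: "This is a reason for stopping therapy, but is NOT objective PD".

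The response window is also stated twice. Section 9.1 uses the first 9 months. Appendix 2, section 3 says: "All participants will have their BEST RESPONSE from the start of study treatment until the end of treatment classified as outlined below".

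**The concern.** The primary endpoint can take two values from the same data, and the protocol does not say which is primary or how a randomised but non-evaluable patient is counted. An analysis plan could follow one section only by departing from the other. In an open-label trial the choice should not remain open once responses are known.

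The two versions also differ in a predictable direction. Membership of the evaluable set depends on what happens after randomisation: staying on treatment for a cycle and being re-scanned. Removing non-responders from a denominator can only raise the proportion. Because the design is non-comparative, the absolute Arm B proportion is the main result, and no between-arm contrast would offset such a bias.

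**Working it through.** **1. Who is counted under each rule**

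| Patient | 9.1 with Appendix 2, section 1 | 13.2 |
|---|---|---|
| At least one cycle and re-assessed | in | in |
| Objective progression before the end of cycle 1 | in | in |
| Stops in cycle 1 for toxicity, preference or symptomatic deterioration, no objective progression | out | in |
| Dies in cycle 1 without objective progression | out | in |
| Never treated, or never re-scanned | out | in |

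A cycle is 56 days in both arms (note to the study schema). In Arm B it contains the first regorafenib course, which follows the 28-day imatinib block (section 7.1). Imatinib taken before randomisation, up to 25 days, counts towards cycle 1, so the part of the cycle after randomisation can be as short as 56 − 25 = 31 days.

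**2. The plan's own figures**

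Section 13.1 gives minimum responses among 38 patients for true rates of 30, 40, 50 and 60%, on a one-sided 95% interval: 7, 10, 13, 17. The exact binomial rule takes the smallest r with P(X ≤ r | n = 38, p) > 0.05 and gives 7, 10, 14, 18. At 50%, P(X ≤ 13) = 0.036; at 60%, P(X ≤ 17) = 0.041; both fall below 0.05. The first two entries are reproduced and the last two differ by one response. The synopsis says the values were taken from published charts. This small difference is a separate matter and does not affect the present point.

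**3. Effect of the denominator**

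If k further randomised patients are non-evaluable and none responds, then

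rate among all randomised = r / (38 + k) = (r / 38) × 38 / (38 + k).

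Both r = 23 and k are assumptions; the protocol gives neither. Differences are taken from unrounded values.

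| k | Rate among all randomised | Exact two-sided 95% CI | Below 23/38 by |
|---|---|---|---|
| 0 | 23/38 = 60.5% | 43.4 to 76.0% | 0 points |
| 2 | 23/40 = 57.5% | 40.9 to 73.0% | 3.0 points |
| 4 | 23/42 = 54.8% | 38.7 to 70.2% | 5.8 points |
| 6 | 23/44 = 52.3% | 36.7 to 67.5% | 8.3 points |

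With 17 responders the same k = 2, 4, 6 lower the rate from 44.7% to 42.5%, 40.5% and 38.6%.

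**4. Effect on the minimum-response table**

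The exact rule of step 2 at other sample sizes gives:

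| n | 30% | 40% | 50% | 60% |
|---|---|---|---|---|
| 38 | 7 | 10 | 14 | 18 |
| 40 | 7 | 11 | 15 | 19 |
| 42 | 8 | 12 | 16 | 20 |
| 44 | 8 | 12 | 17 | 21 |

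The printed minima belong to n = 38 and cannot be carried over to a larger randomised number.

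**The case against.** Several points on the other side have force.

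*Early failures are not all lost.* A reader might infer that the evaluable set drops everyone who fails early. It does not: objective progression before the end of cycle 1 keeps a patient in. The loss is confined to the last three rows of the first table.

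*Arm B is not shown to be worse affected.* A reader might infer that the bias falls mainly on the regorafenib arm. The rule applies to both arms. Section 14.2 asks the monitoring committee to watch drop-out, especially in the experimental arm, but gives no rate. The only discontinuation figures, in section 2, are 6% on regorafenib against 8% on placebo for adverse events, in later-line patients. Regorafenib starts on day 29, so a stop that follows a full 28-day hold falls at day 57 or later. Other cycle 1 exits remain possible, so a larger effect in Arm B is plausible but unquantified.

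*Inflation is likely, not certain.* CT continues until progression after treatment stops, so a patient with less than one cycle could later respond. Section 9.1 does not say whether such a patient enters the numerator. If 2 of 4 non-evaluable patients did respond, the all-randomised rate would be 25/42 = 59.5%, one point below 60.5%.

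*No conclusion is shown to change.* Section 13.1 calls the measured activity primarily descriptive and there is no pass/fail rule. In the illustration, 23 responders exceed every minimum in step 4.

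*The response window.* A reader might infer that 9.1 inflates Arm B by crediting responses to later off-protocol treatment. The two windows do differ, but the documents give no basis for a size. Whether responses after new therapy should count is a choice on which statisticians reasonably differ, and counting them fits an all-randomised analysis.

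These points limit the size and reach of the concern. None removes the contradiction between 9.1 and 13.2.

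**Conclusion.** The contradiction stands as written: two sections give different denominators for the primary endpoint and neither is named as primary. The evaluable version conditions on events after randomisation and is likely to overstate the response rate in whichever arm has cycle 1 losses without objective progression.

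The amount is unknown. It is zero with no such patients and about 3, 6 and 8 points with 2, 4 and 6 in Arm B. Those figures rest on an assumed 23 responders, 38 evaluable patients and no responses among the excluded. No arm-specific excess is established. The difference in response window is a separate inconsistency for which no size or direction is claimed.

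**What to change.** - In section 9.1, make all patients randomised to the arm the primary denominator, in line with 13.2. Count patients without any post-baseline assessment as non-responders and classify everyone else from their scans, however long they were treated.
- Make the same change in section 9.3.
- Keep the rate in the Appendix 2, section 1 evaluable set as a labelled sensitivity analysis, and report by arm how many patients are non-evaluable and why.
- Recompute the minimum-response table in section 13.1 and the synopsis for the number actually randomised to Arm B, instead of applying the n = 38 values.
- Separately, reconcile the 9-month window in section 9.1 with the end-of-treatment window in Appendix 2, section 3, and state which governs the primary endpoint.

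The cost is protocol wording and one recalculated table. No extra patients or assessments are needed. The reported rate may be somewhat lower than the evaluable-set rate.
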